### Data collection

Field and specimen collection standard operating procedures were developed and piloted in one urban and one rural kebele. Training manuals including a comprehensive description of all field work and data collection procedures were used to train all study staff. Enumerators with experience in large-scale nutrition-related surveys were recruited and trained on the study procedures. Experienced phlebotomists were recruited and trained on specimen collection and processing in the field. A supervision plan was developed to maximize data quality.

In each survey, trained enumerators will visit participating households selected during the sampling process to enroll participants and obtain informed consent. For each participant, the enumerators will seek written informed consent for a blood draw to assess serum biomarkers of anemia and a stool specimen to screen for soil-transmitted helminth infections. After enrolling participants on the first visit, the enumerators will return on a separate occasion to administer the questionnaires and collect biological specimens from the woman selected from that household and also the man or child (if applicable for that household). If one of the study participants is not available at the time of interview, the enumerator will return to the household up to three times to complete the assessments and collect the biological specimens. If the participant is still not available after three visits, that participant will be excluded. Table 1 provides an overview of data that we plan to collect for each man, woman and child. All questionnaires and dietary assessments will be administered on tablets using an electronic data collection platform, SurveyCTO (developed by Dobility, Inc.). During the survey, data will be continuously uploaded and monitored for quality.

**Table 1 Tab1:** Questionnaire and biological assessments administered to women, children and men in the Anemia Etiology in Ethiopia (AnemEE) survey

Assessments	Women of reproductive age (15–49 years)	Children^a^ (6–59 months)	Adult Men (15–49 years)
Education, employment and other sociodemographic characteristics	X		X
Water, sanitation and hygiene	X		
Household characteristics	X		
Food fortification	X		
Pregnancy	X		
Morbidity in past 2 weeks	X	X	X
Household food sources	X		
24 h recall	X	X	X
Food frequency questionnaire	X	X	
Anthropometry (weight, height, MUAC)	X	X	X
Blood pressure	X		X
Hemoglobin	X	X	X
Malaria rapid diagnostic test	X	X	X
Soil-transmitted helminths	X	X	X
Ferritin^b^	X	X	X
C-reactive protein^b^	X	X	X
Folate^b^	X	X	X
Vitamin B-12^b^	X	X	X

^a^questionnaires completed on behalf of the child by the child’s primary caregiver

^b^We will attempt to obtain serum from all men, all children and a subset of women (approximately 50%)

#### Demographic, environmental, and socioeconomic indicators

Questionnaires were developed with input from stakeholders to assess individual and household demographic and economic indicators including (but not limited to): age, education, water source and quality, sanitation, employment, household assets, birth history, khat use (chewing of leaves to produce amphetamine-like effects), smoking status, pregnancy status, and other potential demographic, environmental and socioeconomic determinants of anemia and dietary iron intake. These instruments include questions from the Ethiopia 2016 DHS survey, which will allow for direct comparisons.

#### Dietary assessment

For all children, adult female and adult male participants, dietary intake will be measured with both a 24-h recall and a food frequency questionnaire (FFQ) with a 7-day recall. Based on guidelines described by Gibson [16], we developed a 24-h recall tailored to the unique cultural and dietary characteristics of Ethiopia, and pilot tested it in one urban and one rural kebele. The 24-h recall will be administered in multiple passes, which was shown to maximize recall accuracy for quantification [17]. In the first pass, the respondent reports all food and drink intake for the preceding day. In the second pass, the interviewer probes for details on the time, type and quantity of food or drink consumed. In the third pass, the interviewer asks for detailed recipes and in the final pass, the interviewer reviews all food reported in order, prompting for commonly unreported items, and clarifying uncertainties. In order to calculate within-person variability in dietary intake, in one kebele per region (in each survey), all participants will complete two 24-h recalls, one at the beginning of the survey round and another at the end of survey round. The target number of men, women and children with repeated measurements is 400. For the 24-h recall, Ethiopian food composition tables [18] will be used to calculate nutrient intakes. In cases where certain food items and nutrients are not available in the Ethiopian tables, food composition databases from other countries will be used to supplement the Ethiopian tables.

Dietary intake during the past 7 days will be measured using a food frequency questionnaire (FFQ) for all participants. Participants will be asked a series of questions to determine the number and timing of fasting periods within the previous week, as this may also affect intake of particular nutrients and anemia status. We developed the FFQ based on the food items in the Ethiopian food composition tables and piloted the tool in one urban and one rural kebele. For the FFQ, Ethiopian food composition tables will be used to calculate nutrient intakes for all participants, again supplementing with other food composition tables when necessary [18].

#### Portion size estimation

In designing the 24-h recall and FFQ instruments for this population, we estimated portion size for traditional Ethiopian foods using local reference sizes where appropriate and adapting portion sizes to the specifications of each traditional food. For example, for traditional breads such as a grain-based flatbread known as ‘injera,’ portion size is estimated using counts of folds and fractions of a whole injera. Mixed dishes, such as sauces and stews, are estimated by volume using standard household cooking measures displayed as photographs of bowls and spoons, which are representative of the range of portion sizes commonly consumed in Ethiopia. For whole foods and recipe ingredients such as fruits, vegetables and meats, pictures of different sizes of the food item are displayed as portion size options. Three to five sizes of each food are displayed based on the variety of sizes available at local markets. Photographs of the cooking/serving utensils (bowls, spoons, cups, etc.) and whole foods were taken using standardized methodology and including reference objects to maximize accuracy of portion size estimation based on the photographs [19]. For analysis of both the 24-h recall and FFQ, the reported portion size (estimated volume or number of food items consumed) will be converted into grams, for use in calculation of nutrient intake.

#### Anthropometry

Height (or length for children under 2 years of age), weight, and mid-upper arm circumference (MUAC) will be measured for all participating children, women and men. All measurements will be collected in triplicate and recorded electronically on the tablets. Child height/length-for-age (HAZ/LAZ), weight-for-height/length (WLZ/WHZ), and weight-for-age (WAZ) z-scores will be calculated using the WHO child growth 2006 standards [20]. Body mass index will be calculated for adult men and women.

#### Blood and stool collection

Trained field workers will collect venous blood and stool at the household from all women of reproductive age, men and children included in the survey. Two mL of blood will be collected from all men, women, and children in a lavender top vacutainer containing the anticoagulant Ethylenediaminetetraacetic acid (EDTA) for hemoglobin level measurements, malaria rapid diagnostic test (RDT), and dried blood spots. Five mL of blood will be collected in a red top vacutainer (without anticoagulant) from all men (with a target of 7 men per kebele), all children (with a target of 10 children per kebele) and a subset of women of reproductive age (with a target of 9 out of the 17 women participating in the study per kebele). Blood samples will be transported in an ice box from the household to a mobile lab where red top vacutainer samples will be centrifuged and aliquoted to store serum in cryovials within 2 hours and 30 min of collection. Serum samples will be stored in a portable − 20 °C freezer and will be transported to a central regional lab within 24 h. Samples will be shipped to International Clinical Laboratories (ICL) in Addis Ababa once per week for assessment of biomarkers and subsequent storage at − 80 °C. Stool samples will be preserved with 10% formalin within 2 hours of collection. These methods are consistent with methods used in the ENMS [14].

#### Hemoglobin and biomarkers assessment

For all participants, venous blood from lavender-top EDTA tubes will be drawn to assess hemoglobin concentration using a Hemocue HB 201+ analyzer. Hemoglobin levels will be adjusted for altitude, sex, and smoking status to determine anemia status [21]. All participants found to be anemic will be referred to a Health Extension Worker and health center for management that adheres to Ethiopian national guidelines. Stored serum samples will be tested for ferritin, C-reactive protein (CRP), folate and vitamin B12 by ICL in Addis Ababa.

#### Malaria, soil-transmitted helminth and morbidity assessment

The presence of malaria parasites will be assessed by a RDT from lavender-top EDTA tubes. All participants with parasitemia will be referred to the Health Extension Worker and health center for management that adheres to Ethiopian national guidelines. All participants will be asked about the presence and frequency of diarrhea, fever, vomiting, difficulty breathing and signs and symptoms of morbidities in the last 2 weeks. We will also collect information on any hospitalizations and medications taken in the last 2 weeks.

Stool samples will be collected from all children, adult females, and adult males. For each stool specimen, two Kato–Katz slides will be prepared and examined by microscopy for Ancylostoma duodenale (hookworm), Ascaris lumbricoides (roundworm), and Trichuris trichiura (whipworm) ova to determine the presence and intensity of infection.

### Statistical analysis

Anemia will be defined by standard hemoglobin definitions by sex and age (Hb < 11 g/dL for children; < 12 g/dL for non-pregnant adult women; < 13 g/dL for adult men). All hemoglobin levels will be adjusted for altitude, sex, and smoking status [21]. Ferritin will be used to assess iron status. All ferritin levels will be corrected for inflammation using the Biomarkers Reflecting Inflammation and Nutritional Determinants of Anemia (BRINDA) regression correction method [22]. We also will examine the prevalence of iron excess using adjusted serum ferritin concentrations [23]. All prevalence estimates will be calculated by region, urban/rural residence, sex, season, and age and take into account the sampling design.

Risk factors for anemia will be examined for anemia, IDA, and excess iron using generalized linear models taking into account the sampling design and clustering to calculate relative risks [24]. Potential differences in magnitude of risk (effect modification) by age, sex, gender, season, region, urban/rural residence and other factors of interest will be examined.

Population attributable risk percent (PAR%) will be calculated for each risk factor to estimate the percentage of anemia cases that can be independently attributed to that specific risk factor in the population [25, 26]. The PAR% will be used to estimate the percentage of anemia cases that would have been avoided in our study population if a specific risk factor was eliminated. These PAR% estimates will be useful for prioritization in the design of anemia control programs, as they take into account both the prevalence of risk factors and the magnitude of the risk for anemia.

## Discussion

Anemia remains a public health challenge in Ethiopia and prevention and evidence-based treatment strategies are urgently needed. However, there is a lack of information on anemia etiology, hindering the development of evidence-based anemia control efforts. To address the current evidence gaps, we designed the AnemEE survey to evaluate anemia etiology in Ethiopia. This cross-sectional survey in six regions of Ethiopia includes detailed assessment of usual dietary intake through the use of both a 24-h recall and FFQ, anemia and iron biomarkers, soil-transmitted helminth infections, malaria, and inflammatory biomarkers among a population representative sample of men, women, and children. These data are intended to determine the relative contributions of the underlying causes of anemia in order to guide high-impact and safe anemia control intervention programs and policies. To provide further guidance, we will also simulate the impact of introduction of iron fortification and other potential interventions on anemia and iron overload.

Although previous population-based studies in Ethiopia have assessed anemia, AnemEE is unique in that it assesses both anemia and risk factors simultaneously, enabling us to examine anemia etiology. AnemEE will also give us the ability to investigate the effect of seasonality on iron intake and anemia prevalence. Additionally, AnemEE has both consumption data and biological markers of anemia and iron status, which will allow us to estimate the effect of simulated dietary interventions on anemia and iron levels. The ENFCS simulations predicted that excessive iron intake would occur in adults and children in almost all regions if universal fortification of flours or oils were implemented, but this survey only had data on consumption and as a result could not model effects on anemia and excess iron [12]. Furthermore, we will also examine the effects of other health interventions such as deworming and improved sanitation, on reducing the prevalence of anemia and the risk of iron overload.

In light of the limited dietary assessment tools available for Ethiopia, the dietary assessment methods used in AnemEE are a strength of the study, and documenting the operational process of developing and implementing these methods can inform future studies and efforts to advance dietary assessment in Ethiopia. In order to formulate evidence-based nutritional strategies and policies aimed at ensuring adequate nutrient intake, evaluation and validation of reliable dietary assessment methods is important. Although several methodologies to measure dietary data exist, they have had variable success to collect valid dietary data and there is very limited information on their use in Ethiopia [27–31]. Additionally, there are currently no peer-reviewed publications from large-scale surveys in Ethiopia to enable replication of the methods used for dietary assessment. Thus, standardized measures to collect valid dietary data and biomarkers are needed to address the gaps in measuring dietary nutrient intake in Ethiopia. The electronic data collection system and portion size estimation methods used in AnemEE are novel in this context, and can be used to strengthen dietary assessment in future studies.

AnemEE will provide the most comprehensive evaluation of anemia etiology in Ethiopia to date, which will contribute to the evidence base and fill current knowledge gaps regarding prevalence and causes of anemia in Ethiopia. Currently, there is not sufficient evidence to develop high-impact and safe anemia control efforts; therefore, generating data on anemia etiology and simulating potential interventions is critical to inform anemia control programs and policies in Ethiopia.

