### Study population

AnemEE will be conducted in six regions of Ethiopia: Amhara, Tigray, Oromia, Addis Ababa, Afar and Southern Nations, Nationalities, and Peoples’ Region (SNNPR). These regions were selected due to differences in their agroecology, anemia prevalence, and potential for iron overload. In addition, these regions cover a range of agrarian, urban/rural and pastoralist communities. Children (aged 6–59 months) and adult women of reproductive age (15–49 years) are included in the study population due to known high risk of anemia and poor health outcomes. Adult men are included as iron overload is a concern if an iron fortification intervention were to be implemented. Due to differences in diet between seasons in Ethiopia, the survey will be repeated in 2 rounds; the first during the short Belg season (dry season February–April) and the second in the major Meher season (wet season May–September). Both survey rounds will be conducted in the same kebeles (the smallest administrative units in Ethiopia), but the second round will be conducted in a different quadrant of each kebele so that each survey includes different individuals.

A stratified two-stage sampling method will be used to obtain regionally representative samples of urban and rural children and adult women and men in each region in each of the two seasons **(**Fig. 1**)**. In the first stage, two zones from each region will be randomly selected, and within each zone, 3 woredas (districts that collectively make up a zone) will be selected **(**Fig. 2**).** Within each woreda, administrative data from the regional and district administrative offices will be used to randomly sample 2 kebeles (12 kebeles total per region). In the second stage of sampling, each kebele will be divided into quadrants and a central zone, and one of these five areas will be randomly selected. Within each selected area, random households will be visited until 30 eligible households are identified, which will each include at least one woman of reproductive age. Of these, a simple random sample of 17 households per kebele will be selected for participation in the study using computer generated random numbers. Of the 17 households in each kebele, 17 women aged 15–49 years (one per household), 10 children aged 6 to 59 months (no more than one per household) and 7 men aged 15–49 years (no more than one per household) will be included in the study.

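### Men (and children) can be sampled only from households with a woman aged 15–49, so the claim of a population-representative sample should be narrowed to that population.

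*Protocol article*

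**What the plan says.** Three places in the protocol article claim representativeness for men without a qualifier.

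- Study population promises "regionally representative samples of urban and rural children and adult women and men in each region", in each of the two seasons.
- Sample size says the planned number will give regionally representative anemia estimates for children, women and men.
- Discussion describes the data as collected "among a population representative sample of men, women, and children".

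Primary objectives likewise sets the aim for men aged 15–49 in the six regions, with no restriction on household type.

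The selection steps are in Study population. In the chosen part of each kebele, "random households will be visited until 30 eligible households are identified, which will each include at least one woman of reproductive age". From those 30, "a simple random sample of 17 households per kebele will be selected for participation in the study". The 17 households supply 17 women (one each), 10 children and 7 men, with at most one child and at most one man per household. No other route into the sample is described for men or children.

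Data collection adds that specimens and questionnaires are taken from the selected woman and "also the man or child (if applicable for that household".

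Statistical analysis says that prevalence estimates and risk models will allow for the sample design. It does not restrict the men's results to men who live with a woman aged 15–49.

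**The concern.** Household eligibility is defined through the woman. For women this costs nothing, because any woman aged 15–49 lives in a household that contains one. For men it removes part of the stated target population before sampling begins: men living alone, men in all-male households, and men living only with girls under 15 or women over 49. Children aged 6–59 months in households without a woman aged 15–49 are removed in the same way, though such children are presumably few.

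This matters most for men. Study population says they are included because iron overload is a concern if iron fortification is introduced. Household composition may plausibly relate to diet, so the missing men could differ on the outcome for which men were added. Prevalence, risk-factor and simulation results for men are meant to guide safe control programs. A reader told that the sample represents men in the region would apply them to all men.

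**Working it through.** **1. Reproduce the plan's own total.** Inputs from Study population: 17 women, 10 children and 7 men per kebele; 2 zones × 3 woredas × 2 kebeles = 12 kebeles per region; 6 regions; 2 rounds.

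(17 + 10 + 7) × 12 × 6 × 2 = 34 × 144 = 4896.

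This is exactly the calculated figure in Sample size. The planned number is therefore filled entirely from the 17 sampled households per kebele and leaves no room for men recruited by another route. (The total was then raised to 5100 for precision; no separate source of participants is mentioned.)

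**2. Trace a man's selection probability.** Eligible households are those with a woman aged 15–49; 17 of 30 are drawn; men come from the 17. For a man in a household without such a woman, the probability of eligibility is 0, so his overall probability is 0. A design weight is the inverse of the selection probability and does not exist for him.

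**3. Form of the bias.** Let f be the share of men aged 15–49 who are uncovered, and let p_c and p_u be the prevalence in covered and uncovered men.

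Bias = p_c − [(1 − f)p_c + f·p_u] = f(p_c − p_u).

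The document gives neither f nor p_u, so these are assumptions:

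- f = 10%, difference 5 points: 0.10 × 5 = 0.5 points.
- f = 30%, difference 10 points: 0.30 × 10 = 3.0 points.

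The sign depends on p_u. With p_c = 18% (the national figure for men in Background) and f = 30%, p_u = 28% gives −3.0 points and p_u = 10% gives +2.4 points. The sample size does not appear in the formula.

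**4. Compare with sampling error.** Half-width = 1.96 × √(2.0 × 0.18 × 0.82 / n), using the design effect from Sample size.

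| Men | n | 95% half-width |
|---|---|---|
| One region, one round | 7 × 12 = 84 | 11.6 points |
| One region, both rounds | 168 | 8.2 points |
| Six regions, both rounds | 1008 | 3.4 points |

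The assumed bias is well below regional sampling error. Its upper end is comparable with the pooled half-width.

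**5. Man or child in a household.** 10 + 7 = 17, the number of households, which fits one man or one child per household but does not prove it. For illustration, suppose child places were filled first and a share q of the 17 households had an eligible child. The share of the 7 remaining households with a child would be (17q − 10)/7: 15% for q = 65%, 39% for q = 75%, 76% for q = 90%. If man or child were instead assigned at random, men living with children would keep a known, non-zero chance of selection that a weight can handle.

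**The case against.** The strongest reply is that this is only a matter of scope. Household surveys often enter through one index member, the analysis will allow for the sample design, and any plausible bias is small beside the regional uncertainty. Statistical analysis also words its avoided-cases interpretation of PAR% as applying to the study population, not to all men in a region. The points about size and PAR% stand, and they limit how serious the matter is. The point about the analysis does not: weighting corrects unequal probabilities, not zero ones, and three sections state a property that the sample lacks.

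A reader might infer more than the document supports, in three ways.

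- *Men living with young children are excluded.* No section says that a household supplying a child cannot also supply a man. The one-per-household limits are given separately for each group, and the man-or-child phrase may simply describe whom the enumerator returns to see. Even under an exclusive rule, a household where no child was sampled need not be a household without children. The missing assignment rule is a detail that an article may leave to the full protocol.
- *There is a bias of 0.5–3 points in every region.* Both inputs are assumed, and nothing suggests that they are equal in, say, Addis Ababa and Afar. No size can be given for iron excess at all.
- *Men should be redrawn from all screened households.* Enrollment began on January 27, 2019, data collection was expected to run through August, and recruitment was still open on August 6. A change of frame that late would mix two kinds of male sample and confound the comparison of seasons. Households without an eligible woman are not said to be listed. Table 1 takes household, water and sanitation data only from women, so added men would lack them.

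**Conclusion.** The point holds as an error in the stated target population. The design represents men and children living in households with a woman aged 15–49, whereas the article claims men and children of the region. This follows directly from the eligibility rule and needs no assumption.

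The consequence for the estimates is unknown in size and direction. The range of about 0.5–3 points rests wholly on assumed values for the uncovered share (10–30%) and the prevalence difference (5–10 points). It is small against 8.2 points per region and at most similar to 3.4 points pooled. That supports correcting the claim, not discarding the men's results or resampling.

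**What to change.** 1. In Study population, Sample size and Discussion, describe the target for men and children as those of the stated ages living in a household with at least one woman aged 15–49. The description of women can stay.
2. Limit the conclusions on men's anemia, iron excess, PAR% and simulated interventions to that population.
3. List as a limitation that men in households without a woman aged 15–49 could not be selected, that weighting does not correct this, and that the size and direction of any effect are unknown. Note that the same applies to children, probably with less effect.
4. If each household supplies either a man or a child, make the selection weights for men and children reflect how households were assigned.

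The first three items cost only wording. The fourth needs the assignment rule that was used in the field and a corresponding factor in the weights. No new data collection is required.
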